## Abstract

**Background:**

Mechanisms influencing breast cancer (BC) development and recurrence include hyperglycemia, hyperinsulinemia, high insulin-like growth factor-1, high circulating estrogen, inflammation and impaired cellular differentiation/apoptosis. A lifestyle program that targets all the above mechanisms may be warranted. Low glycemic index (GI) foods produce lower post-prandial glucose and insulin responses and have been associated with lower BC risk. Moderate physical activity post-diagnosis reduces BC recurrence and mortality, partly explained by reduced insulin and estrogen levels. Vitamin D increases cell differentiation/apoptosis and high serum vitamin D levels improve BC survival. Yet no trial has evaluated the combined effect of a low GI diet, moderate physical activity and vitamin D supplementation on BC recurrence in the context of a Mediterranean lifestyle setting.

**Methods:**

Women (30-74 yr) who had undergone surgery for primary histologically confirmed BC (stages I-III) within the previous 12 months, in cancer centres in Italy, will be randomized to follow, for a maximum of 33 months, either a high intensity treatment (HIT) composed of low GI diet + exercise + vitamin D (60 ng/mL serum concentration) or a lower intensity treatment (LITE) with general advice to follow a healthy diet and exercise pattern + vitamin D to avoid insufficiency. Both interventions are on a background of a Mediterranean diet. Considering a 20% recurrence rate within 3 years for BC cases and a predicted rate of 10% in the HIT group, with power of 80% and two-sided alpha of 0.05, the subject number required will be 506 (*n* = 253 in each arm). Clinic visits will be scheduled every 3 months. Dietary and exercise counselling and vitamin D supplements will be given at each clinic visit when blood samples, anthropometric measures and 7-day food records will be collected.

**Discussion:**

DEDiCa study aims to reduce BC recurrence in women with BC using a lifestyle approach with additional vitamin D and to investigate possible cardio-metabolic benefits as well as epigenetic modifications according to lifestyle changes. Given the supporting evidence and safety of the components of our intervention we believe it is feasible and urgent to test it in cancer patients.

**Trial registration:**

May 11, 2016; NCT02786875.

**EudraCT Number:**

2015-005147-14

## Background

Breast cancer (BC) is the most common cancer in women and the 5-year survival rate in Europe is 82% suggesting a considerable residual risk [1]. BC is associated also with other chronic conditions including type two diabetes which may increase the risk of BC recurrence [2–4] and many BC patients are at increased risk for cardiovascular disease (CVD) [5, 6]. Mechanisms of BC appear to be linked to sex hormones, impairment in glucose metabolism, hyperglycemia, hyperinsulinemia, insulin-like growth factors (IGF), inflammation, oxidative stress and impaired cell apoptosis [7, 8]. Current advice to BC survivors suggests adopting cancer prevention strategies [8, 9], however there is no consensus on the effectiveness of lifestyle programs in women with BC [10–12] mostly due to lack of sufficient evidence [13]. The rationale for the study is to target several mechanisms of cancer suppression or proliferation, with a healthy diet and exercise program, to avoid low vitamin D levels in order to obtain maximal efficacy of the lifestyle program, and concomitantly to offer maximal CVD and diabetes protection. Dietary carbohydrates are the main food components to affect glycemia and insulinemia. The glycemic index (GI) is able to capture the difference between those that increase glycemia the most (high GI foods) and those that increase it the least (low GI foods) [14]. Low GI foods lower the glycemic and insulinemic potential of the diet and have been shown to reduce the risk of several cancers particularly diabetes-related cancers including BC [15–18] and some evidence suggests they also correlate with lower recurrence [19]. Furthermore, low GI diets have been inversely associated with risk of type two diabetes [15, 20, 21] and CVD [22, 23] and favourably modified blood glucose [24–26], blood lipids [27], inflammatory markers [28], oxidative damage [29], body weight [30] and IGF binding proteins [31], all factors relevant to carcinogenesis, diabetes and CVD. Our previous studies in Italy have shown significant risk reduction of 40% with a low GI diet compared to a high GI diet in BC primary prevention [18]. Physical activity is one of the mainstays of primary prevention of cancer and it is also included in guidelines for BC survivors (at least 150 minutes per week) mainly to reduce complications such as lower muscle strength and risk of depression [13]. However, physical activity after BC diagnosis has also been shown to reduce the risk of BC mortality by 40–50% particularly when it is of moderate intensity such as 30 minutes of brisk walking per day [32–35] an effect possibly modulated partly by insulin economy improvements in reduced insulin, insulin-like growth factors and estrogen levels [36].

To maximize lifestyle changes it may be useful to avoid vitamin deficiencies, particularly vitamin D deficiency which has been linked to higher breast cancer risk [37, 38]. Vitamin D alters genes implicated in cellular growth, affecting proliferation, apoptosis, differentiation, angiogenesis, invasion and metastasis [37]. Preliminary studies suggest that normal-high ranges of serum vitamin D levels improve BC survival [39, 40].

Low glycemic index diet, exercise and vitamin D intake, in addition to determining metabolic changes and benefits for cancer patients, may be able to change the tumor microenvironment and lead to epigenetic modifications [41–44]. In this context, microRNAs (miRNAs), small noncoding RNA molecules, may play a fundamental role in modulating gene expression and breast cancer progression [45, 46]. The evaluation of circulating miRNAs is useful to identify the change of specific miRNAs involved in cancer pathways and predict the development of recurrence in breast cancer patients.

A lifestyle program that targets all the above mechanisms may be warranted. To our knowledge no trial has evaluated the combined effect of a lifestyle program with a healthy diet focusing on low GI, additional physical activity and supplemental vitamin D on BC recurrence and complications in the context of a Mediterranean dietary setting.

## Methods/Design

### Aims and objectives

DEDiCa study aims primarily at reducing BC recurrence in women with BC using a lifestyle approach with additional vitamin D. The primary objective of DEDiCa study is to determine the effect of a 33-month program combining advice on diet, exercise and supplemental vitamin D, on reducing BC recurrence rates or increasing disease-free survival (DFS). Secondary objectives are to improve markers of diabetes risk and management for those who already have diabetes, to improve cardiometabolic health and quality of life (QoL) and to investigate whether changes in microRNA correlate with changes in lifestyle.

### Study design

This is a randomized clinical trial targeting women with BC stages I-III within 12 months from BC surgery (see Tables 1 and 2 for details). The study involves at least five cancer centers in Italy (Table 3) and it started on Oct 10^th^, 2016. Consenting participants are randomized to either a high intensity program (HIT) or a lower intensity program (LITE, positive control). The endpoints will be assessed at baseline and every three months until the end of the study (Fig. 1).

**Table 1 Tab1:** Inclusion and exclusion criteria

Inclusion criteria	Exclusion criteria
1. Women with primary diagnosis of histologically confirmed breast cancer (T1 with Ki67 ≥ 30%, T2, T3 without metastasis) within 12 months from diagnosis. 2. Age ≥ 30 and < 75 years. 3. Patients who are able to comprehend and are willing to sign the consent form and are able to adhere to the protocol including scheduled clinic visits and assigned treatment.	1. Patients who do not possess the inclusion criteria for this study. 2. Patients with sarcoidosis or other granulomatous diseases or with hypercalcemia (Ca > 11 mg/dL). 3. Patients with any previous or current concomitant malignant cancer. 4. Pregnant or lactating women. 5. Patients with AIDS diagnosis 6. Patients with severe renal insufficiency 7. Patients with kidney stones (nephrocalcinosis or nephrolithiasis) 8. Patients participating in other lifestyle clinical trials

**Table 2 Tab2:** Details of inclusion criteria n. 1

Stage	Primary Tumor	Lymph nodes	Metastasis	Ki-67
I	T1b, T1c	N0	M0	≥30%
IIA	T1a, T1b, T1c T2	N1 N0	M0 M0	any
IIB	T2 T3	N1 N0	M0 M0	any
IIIA	T1a, T1b, T1c T2 T3	N2 N2 N1, N2	M0 M0 M0	any
IIIC	T1a, T1b, T1c T2 T3	N3 N3 N3	M0 M0 M0	any

**Table 3 Tab3:** List of recruiting centres in Italy

Recruiting centres
• Coordinating Centre: National Cancer Institute Fondazione G. Pascale (Napoli); ○ [name] ○ [contact] ○ Email: [contact] ○ www.istitutotumori.na.it/ • Clinica Mediterranea, Senology Unit; [name]; www.clinicamediterranea.it/ • Cannizzaro Hospital, Senology Unit; [name]; www.aocannizzaro.it/ • San Vincenzo Hospital of Taormina, Oncology Unit; [name]; www.oncologiataormina.it/ • National Cancer Institute CRO Aviano; [name]; www.cro.it

**Fig. 1 Fig1:**
[figure not shown]
Schematic representation of DEDiCa study protocol

To improve compliance participants on both sides will be followed equally with blood tests and clinic visits and will be equally offered general advice on a healthy Mediterranean diet and physical activity, step counters and vitamin D supplements to avoid insufficiency. Participants in the HIT group will additionally receive dietary counselling on how to reduce the GI of their diet, packages of pasta, more in-depth advice on exercise and more vitamin D supplements compared to the LITE group.

This study was approved by the ethic board of the Italian Medicine Agency (AIFA), and of each recruiting hospital: National Cancer Institute “Fondazione Giovanni Pascale” in Naples, Azienda Ospedaliera per l’Emergenza Ospedale Cannizzaro in Catania, Azienda Ospedaliera Universitaria Policlinico “G. Martino” in Messina for San Vincenzo Hospital of Taormina, Comitato Etico Campania Centro ASL NA1 Centro for Clinica Mediterranea in Naples. The study has been registered with ClinicalTrials.gov (registration date and number: May 11, 2016; NCT02786875).

### Participants

Women who had undergone surgery for primary histologically confirmed BC, stages I-III (see Tables 1 and 2 for details), within the previous 12 months in cancer centres in Italy, who are between the ages 30–74 years and have no contraindications to participate in this study will be eligible to participate. Eligibility is confirmed by central reviewing of medical records and pathology reports. The inclusion and exclusion criteria are summarized in Table 1. To participate in the study each potential participant is required to read and sign the study information/consent form at baseline.

### Recruitment and randomization

Eligible participants are recruited in five oncologic centres in Italy (four in Southern Italy and one in Northern Italy). Details of the recruiting centres can be found in Table 3. Eligible participants are contacted either by phone or during one of their follow-up visits and offered to hear more about the study during an information session (either group session or a one-to-one session to accommodate all needs). Eligible participants are explained the study details and are given an informed consent document to take home which they bring back at the baseline visit. At the baseline visit, after obtaining written consent the participant is sent for a blood test and other measurements, is randomized to one of the two arms of the study, receives the advice on the program according to her randomization arm and is given the next appointment slip. Participants are contacted by phone monthly for the first three months and once between visits afterwards. Study visits are scheduled every 3 months until end of study (33 months).

Randomization is done electronically in real time for all recruiting centres and is stratified by stage (I/IIA vs. IIB/IIIA) and age (<50 yrs or ≥50 yrs) at diagnosis and is based on a permuted block design with block size of 4. Stratification by stage and age is done because we expect these variables to affect the outcomes. To prevent any possible study bias the randomization sequence will be done off-site by a third party statistician (Contract Research Organization, Naples, Italy) who will not have contacts with the study participants. The PI is blinded to the randomization of the study participants but not the staff involved in the clinic visits.

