### Outcome measures

Figure 1 depicts the timing and frequency of all study measures. Blood analyses, blood pressure, anthropometric measurements and 7-day food records are taken at baseline and every 3 months afterwards until end of study (up to 33 months). Complete blood analyses are done at baseline, 1 year and end of study while blood analysis pertinent to the treatment are done every three months (Table 5). The primary outcome is the percentage of patients alive at end of study without BC recurrence (disease in the same or opposite breast or any metastasis). The primary outcome is assessed at each collaborating centre by the collaborating oncologist and confirmed by hospital pathological results which are communicated to the coordinating centre. Secondary end points include glycemic control including blood glucose and glycated hemoglobin (HbA1c), cardiometabolic variables including body weight, waist circumference, body mass index (BMI), blood pressure, C-reactive protein (CRP) and blood lipids, hormonal measures including insulin, insulin-like growth factor-1 (IGF-1), estradiol, testosterone and sex hormone binding globulin (SHBG), and epigenetic markers (microRNA). Program adherence and any difficulty noticed, medications and medication changes, as well as any unusual or adverse events, including illness or stressful issues, that occurred since the last clinic visit are recorded in detail.

**Table 5 Tab5:** Blood analyses performed during the study

Parameters	Baseline, 12 mo and study end	Every 3 months
25(OH)D	x	x
Calcium	x	x
Glucose	x	x
HbA1c	x	x
Insulin	x	
Triglycerides	x	
Total Cholesterol	x	
LDL-C	x	
HDL-C	x	
AST/ALT	x	
CRP	x	
Estradiol	x	
Testosterone	x	
SHBG	x	
IGF-1	x	
microRNA	x	
For future analyses	x	x

*AST/ALT*: aspartate transaminase/alanine transaminase, *CRP*: C-reactive protein, *HbA1c*: hemoglobin A1c, *HDL-C*: high density lipoprotein cholesterol, *IGF-1*: insulin-like growth factor-1, *LDL-C*: low density lipoprotein cholesterol, *SHBG*: sex hormone binding globulin, *25(OH)D*: 25-hydroxyvitamin D.

Blood samples and all information regarding the patient are sent to the coordinating centre where blood samples are centrally analyzed and information entered electronically and statistically analyzed for the interim and end of study reports.

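### A single, published block size of 4, with clinic staff who know the allocations, weakens concealment; undisclosed varying blocks would be a cheap improvement

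*Protocol article*

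**What the plan says.** All of this is in the protocol article.

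- *Recruitment and randomization*: allocation "is based on a permuted block design with block size of 4". The strata are two stage groups crossed with two age groups, split at 50 years, which makes 2 x 2 = 4 as written. Centre is not a stratification factor.
- The same section describes the mechanism: "Randomization is done electronically in real time for all recruiting centres", and "the randomization sequence will be done off-site by a third party statistician". Five centres recruit.
- On blinding: "The PI is blinded to the randomization of the study participants but not the staff involved in the clinic visits". Written consent, baseline measurements, randomization and arm-specific advice follow one another at the baseline visit.
- *Study design*, Table 1, inclusion criterion 3 asks, among other things, for women who "are able to adhere to the protocol including scheduled clinic visits and assigned treatment". No assessor is named.
- *Participants*: eligibility is confirmed centrally from medical records and pathology reports.
- *Outcome measures*: "Blood samples and all information regarding the patient are sent to the coordinating centre". Table 3 shows that this centre also recruits.

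**The concern.** Generating the list off-site and releasing each assignment in real time hides the list. It does not hide what past assignments imply about the next one. With every block of size 4, and the size in print, a person who knows the earlier assignments in a stratum can sometimes work out the next arm and can often guess it.

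At stake is selection at entry. Women are approached by phone or at follow-up visits and may enter up to 12 months after surgery, so there is some latitude over whom to invite and when to book. If that latitude were used with the next arm in mind, the arms could differ at baseline in ways the analysis would not correct. Intention-to-treat analysis keeps women in the arm to which they were randomised, but does nothing about who was put forward. The stratified repeat of the log-rank test (*Primary analyses*) lists time since diagnosis, waist circumference and baseline diet, but not baseline activity or motivation. The article's own Discussion treats activity as prognostic, citing 40–50% lower breast cancer mortality with activity after diagnosis.

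**Working it through.** The plan gives no figure for predictability, so there is none to reproduce. Inputs from the plan: block size 4, four strata, five centres, no centre stratum (*Recruitment and randomization*), and 506 women (*Sample size*), used only as a multiplier.

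**1. Full sight of a stratum: certain assignments.** A balanced block of 4 has 6 possible orders, hence 6 x 4 = 24 positions. The fourth position is always determined (6 of 6). The third is determined when the first two are the same (2 of 6). Certain share = (6 + 2)/24 = 8/24 = 33.3%. As a ceiling over the trial, 506 x 1/3 = 168.7, about 169 assignments.

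**2. Full sight: correct guesses.** Guess the arm that is behind in the block, and toss a coin when the arms are level.
- Position 1: 1/2.
- Position 2: 2 of the 3 remaining places belong to the other arm, so 2/3.
- Position 3: certain with probability 1/3, level with probability 2/3, so 1/3 + (2/3)(1/2) = 2/3.
- Position 4: 1.

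Average = (1/2 + 2/3 + 2/3 + 1)/4 = 17/24 = 70.8%, against 50% by chance.

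**3. Sight of one centre only.** When five centres draw on the same four lists, other centres' assignments fall unseen between a centre's own. Simulation of 506 women (300 repetitions) with assumed stratum shares of 15/35/15/35% and assumed centre shares gave these correct-guess rates:

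| Assumed centre shares | Centre | Guess the arm behind in own count | Guess the opposite of own last allocation |
|---|---|---|---|
| five equal | average | 51.4% | 54.6% |
| 60/10/10/10/10 | largest | 53.6% | 59.9% |
| 60/10/10/10/10 | smaller | 50.7–51.6% | 52.1–52.5% |
| 80/5/5/5/5 | largest | 55.6% | 61.4% |
| 80/5/5/5/5 | smaller | 49.8–51.2% | 50.5–51.4% |

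With equal centres, or at a dominant centre, the range is about 51% to 61%. At small centres beside a dominant one, guessing is close to chance. These are two simple rules, not the best possible ones, and the article does not give the centre shares.

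**4. Randomly varying blocks of 4, 6 and 8.** Expected correct guesses per block under the rule in step 2, with full sight and known block boundaries, are 2.83, 4.10 and 5.33. With the sizes equally likely, the rate is (2.83 + 4.10 + 5.33)/(4 + 6 + 8) = 12.26/18 = 68.1%. Simulation using the running imbalance gave 67.9%. The guess rate therefore falls by less than 3 percentage points. The gain lies elsewhere: without knowing where a block ends, an observer can rarely be certain of the next assignment.

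**5. Price in balance.** The largest within-stratum imbalance is half the block size: 4/2 = 2 now, and 8/2 = 4 with blocks up to 8. Over four strata the worst case is 4 x 2 = 8 now and 4 x 4 = 16 then, among 506 women.

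**The case against.** The strongest reply is that the trial already has the main safeguards: an off-site third-party list, real-time electronic release, consent before randomization and central confirmation of eligibility. Leaving centre out of the strata is itself protective, because it breaks up the sequence that any one site sees. On this view the 33% and 71% figures describe an observer who may not exist, and varying blocks barely change the guess rate. Most of this stands. It reduces the point to a modest weakness but does not remove it: past allocations are known to the people who run the visits, and the block size is fixed and in print.

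Two stronger readings are tempting, and the article supports neither.

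- A reader might infer that unblinded staff apply criterion 3 against the arm they foresee, and so steer entry. The article does not say who applies the criterion. *Participants*, *Recruitment and randomization* and *Interventions* place eligibility and consent before allocation, so the reference to assigned treatment most naturally means whichever arm is drawn. The central review does not visibly cover ability to adhere, but that does not show misuse.
- A reader might infer that the coordinating centre, which recruits and receives every centre's data, can follow the arm counts in each stratum. *Outcome measures* describes data and samples sent for central analysis, data entry and reporting. It does not say that recruiters there see allocations by stratum, in order, before the next woman is randomised.

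**Conclusion.** The point holds as a weakness in concealment, not as evidence of steered entry. With a fixed, disclosed block size of 4 and clinic staff who know the allocations, the predictable share is at most 33% certain and 71% guessable. Reaching that ceiling needs sight of every earlier allocation in a stratum, which the article attributes to no one. The figure of about 169 assignments is the same theoretical ceiling and should not be read as an expected number. For staff who see only their own centre, about 51% to 61% is the more realistic range. It rests on assumed centre and stratum shares, on two simple guessing rules, and on the five centres sharing each list, as the stated strata imply. No size or direction of bias in disease-free survival can be derived from the document. This is a cheap improvement.

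**What to change.** In *Recruitment and randomization*, for women still to be randomised, replace the fixed block with randomly varying block sizes (for example 4, 6 and 8), and state that the sizes are not disclosed to the centres. The existing third-party statistician can issue the new list. Starting it in each stratum once the open block of 4 is complete keeps the within-stratum imbalance to at most 4.

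Optionally, reword criterion 3 in Table 1 to ask for women able and willing to follow either programme, since the arm is not known when eligibility is judged. This is a clarification, not the correction of an error.

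The cost is one new list, one changed sentence and, if wanted, one line in Table 1. The downside is the rise in possible within-stratum imbalance from at most 2 to at most 4. The benefit should be described as removing most certain knowledge of the next allocation, not as making allocation unguessable.

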### Interventions

Eligible and consenting subjects are randomized to either one of the two treatment programs (higher or lower intensity):
**Higher intensity (HIT) arm (test)**: low GI diet + exercise + vitamin D.All carbohydrate foods advised will be low GI choices (GI < 70, on the bread scale), e.g. legumes, pasta al dente, barley, low GI rice, low GI bread, oat, apples, oranges, berries, avocado and nuts.Brisk walk of at least 30 min per day (or approximately 5000 steps) more than the habitual physical activity.Vitamin D supplement (cholecalciferol) up to 4000 IU/day to reach the upper end of normal blood levels of 25(OH)D (60 ng/ml).

Lower intensity (LITE) arm (positive control): general recommendations for a healthy diet and physical activity. Vitamin D (cholecalciferol) will be given only if hypovitaminosis D is detected to bring blood levels up to normal ranges of 30 ng/mL.

Both groups will be counselled to follow a healthy Mediterranean diet (≥5 servings vegetable/fruit per day, ≤1 serving red meat/cold cuts per week, <7% saturated fat).

Treatment evaluations are conducted every three months at each clinic visit and include all three components of the treatment (diet, exercise, vitamin D). Seven-day food records is collected from each patient which is filled a week before the clinic visit. The information in the food record is reviewed by the nutritionist staff with the patient and subsequently inserted in a diet analysis program (WinFood Medimatica, Version 3.9.0). Daily means of GI, energy intake, macro- and micro-nutrients and food groups will be obtained from WinFood and periodically evaluated to ensure adherence to the dietary advice. The physical activity component is measured with a step counter with 7-day memory (OMRON Walking Style IV) and with a questionnaire. Participants bring the step counter back at each clinic visit and the 7-day values are recorded by the research staff. Vitamin D is evaluated by blood analysis of 25(OH)D every three months, the dose reviewed at each clinic visit and changed if necessary to reach the group target (Table 4). QoL is measured with questionnaires specifically made for cancer patients (EQ-5D-3 L, EORTC QLQ-C30 e EORTC QLQ-BC23) [47–49].

**Table 4 Tab4:** Vitamin D algorithm

Blood levels (ng/ml)	Oral dose (IU)	Treatment duration
Group A (target: 60 ng/ml):		
< 10	75 000 at study visit +4000/day	3 months then re-evaluate
> 10-20	50 000 at study visit +4000/day	3 months then re-evaluate
> 20-30	25 000 at study visit +4000/day	3 months then re-evaluate
> 30	4000/day	3 months then re-evaluate
60-80	change to 1000 IU/day	3 months then re-evaluate
Group B (target: 30 ng/ml):		
≤ 10	100 000 at study visit	Re-evaluate after 3 months
≤ 20	75 000 at study visit	Re-evaluate after 3 months
> 20-25	50 000 at study visit	Re-evaluate after 3 months
> 25-29	25 000 at study visit	Re-evaluate after 3 months
≥ 30	0	Re-evaluate after 3 months

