### Potential toxicity and adverse events

Toxicity due to diet, moderate exercise or vitamin D supplementation are not expected. The diet is an enhanced Mediterranean diet with one arm consuming more low GI foods and physical activity involves moderate exercise of 30 min of daily brisk walk and both respond to lifestyle principles suggested by cancer guidelines such as the American Cancer Society [8] and the World Cancer Research Fund [9]. Oral vitamin D (cholecalciferol) supplementation will be given at safe dosages (up to 4000 IU/day) to reach safe blood levels (60 ng/ml for the test arm and 30 ng/ml for the control arm) [53, 54]. In Italy the normal range of 25(OH)D is between 30-100 ng/ml. Excess vitamin D levels (>100 ng/ml) could induce excess calcium absorption from the intestine and potentially result in hypercalcemia (>11 mg/dl). Both serum 25(OH)D and calcium levels are monitored throughout the study at each clinic visit and any signs or symptom of hypervitaminosis D (hypercalcemia, excess thirst, etc.) will be recorded and immediately communicated to the participant’s physician and supplementation stopped. All adverse events occurring after signing the consent form will be recorded in a specific Adverse Event Form.

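### Table 4 gives no correct printed vitamin D dose for a Group A woman whose 25(OH)D is above 80 ng/ml

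*Protocol article*

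**What the plan says.** The Interventions section of the protocol article describes the high-intensity dose as "Vitamin D supplement (cholecalciferol) up to 4000 IU/day to reach the upper end of normal blood levels", with 60 ng/ml as the figure aimed at. It makes Table 4 the operating rule: 25(OH)D is measured every three months, with "the dose reviewed at each clinic visit and changed if necessary to reach the group target (Table 4".

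Group A in Table 4 has five rows:

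| 25(OH)D, ng/ml | Dose |
|---|---|
| < 10 | 75,000 IU at the visit, plus 4000 IU/day |
| > 10-20 | 50,000 IU at the visit, plus 4000 IU/day |
| > 20-30 | 25,000 IU at the visit, plus 4000 IU/day |
| > 30 | 4000 IU/day |
| 60-80 | "change to 1000 IU/day" |

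No Group A row follows the last one. Group B, by contrast, ends with an open row (30 or more, dose 0).

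The section on potential toxicity and adverse events says "Oral vitamin D (cholecalciferol) supplementation will be given at safe dosages (up to 4000 IU/day", with blood levels of 60 and 30 ng/ml as the safe targets. It adds "In Italy the normal range of 25(OH)D is between 30-100 ng/ml" and "Excess vitamin D levels (>100 ng/ml) could induce excess calcium absorption from the intestine". Supplementation is stopped for signs or symptoms of hypervitaminosis D, and the examples given are hypercalcemia and excess thirst. The Discussion places toxicity above 150 ng/ml.

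**The concern.** A dosing table that staff apply at several centres for up to 33 months should give one dose for every result. It matters most at the top of the scale, where a woman is already over target and the direction of the dose change is a safety question. Here the printed rows give either a dose in the wrong direction or none. Two centres could treat the same result differently, and the three-monthly measurement protects a participant only if the result leads to a defined action.

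A smaller point lies next to it. The safety sentence gives 4000 IU/day as the upper dosage, while three Group A rows add a large single dose at the visit. Someone who reads only the safety section would not learn of these doses.

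**Working it through.** **1. Apply the Group A rows as printed.** The inputs are the five rows of Table 4.

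| Level, ng/ml | Rows that match literally | Daily dose |
|---|---|---|
| 35, 59 | > 30 | 4000 IU |
| 60, 70, 80 | > 30 and 60-80 | 4000 or 1000 IU |
| 81, 90, 100, 110, 150 | > 30 only | 4000 IU |

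The double match at 60-80 is resolved by the word change in the last row, which steps down from 4000. That implies the > 30 row was meant to end at 60. With that bound applied, levels of 81 and above match no row at all. These are the only two readings, and neither yields a usable dose.

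**2. Size of the ambiguity.** The two printed daily doses differ by 4000/1000 = 4 times, or 4000 - 1000 = 3000 IU/day. Over a 91-day interval that is 3000 × 91 = 273,000 IU before the next check. A hold would widen the gap to 4000 IU/day.

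**3. Look for a rule elsewhere.**
- Interventions: the dose is to move towards the group target. This gives a direction (down) but no dose.
- Potential toxicity and adverse events: the trigger for stopping is signs or symptoms. The level of 100 ng/ml is named as excess and as a possible cause of hypercalcemia (> 11 mg/dl), but it is not written as a stopping level.
- Outcome measures: "blood analysis pertinent to the treatment are done every three months (Table 5"; Table 5 lists 25(OH)D and calcium among these. This is monitoring, not a dose.

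A woman above 80 ng/ml with normal calcium and no symptoms is therefore covered by none of these. Because no level-based stop is stated, the gap has no printed upper end; it does not close at 100.

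**4. The 4000 IU/day figure.** The highest daily maintenance dose in any Group A row is 4000 IU, so the stated figure is reproduced for maintenance. With visit doses included, the average over one interval is 4000 + L/d, where L is the visit dose and d the days in the interval (3 months taken as 90 to 92 days):

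| L, IU | d = 90 | d = 92 | Above 4000 |
|---|---|---|---|
| 75,000 | 4000 + 833 = 4833 | 4000 + 815 = 4815 | 20-21% |
| 50,000 | 4000 + 556 = 4556 | 4000 + 543 = 4543 | 14% |
| 25,000 | 4000 + 278 = 4278 | 4000 + 272 = 4272 | 7% |

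So in three of the five rows the average intake is about 4270-4830 IU/day.

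**The case against.** The case against is strong on several counts.

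- **Context rules out the alarming reading.** The rows ascend, the group is headed by its 60 ng/ml target, and the last row is a step down. A reader might infer that women above 80 ng/ml would really be put back on 4000 IU/day. The document does not support that as a prediction: doing so would contradict the stated aim of the dose review. This stands. It removes the likely harm, but it does not supply the missing dose.
- **An article condenses a protocol.** The full protocol may hold a rule for levels above 80. That is possible, and the finding does not assert that sites lack one. But Table 4 is printed as a complete algorithm with levels, doses and durations, and its literal application gives a wrong dose. That is a fault in what is printed, not merely a detail left out.
- **The risk is already limited.** Levels of 80-100 ng/ml are inside the stated normal range of 30-100, toxicity is put above 150, and 25(OH)D and calcium are checked every 3 months. This stands.
- **The visit doses are not hidden.** Table 4 prints "75 000 at study visit +4000/day" and the two lower loading doses, and the Interventions text refers to the table. As a daily maintenance figure 4000 IU is correct. This stands, so the safety sentence is a matter of presentation. A reader might infer that the loading doses are unsafe. Nothing in the document shows that: they apply only at 30 ng/ml or below, and for levels under 10 the Discussion cites guidance allowing up to 600,000 cumulatively, against a Group A maximum of 75,000 + 91 × 4000 = 439,000 IU over one interval.

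**Conclusion.** The point holds as a dosing-safety clarification. For any 25(OH)D level above 80 ng/ml in Group A, Table 4 prints either 4000 IU/day, which moves away from the target, or nothing, and no other section supplies a dose for a symptom-free woman with normal calcium.

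It is tempting to describe the gap as a band from 80 to 100 ng/ml. That would treat 100 as a stopping level, which the toxicity section does not make it.

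The practical risk is small. The document does not say how many women would exceed 80 ng/ml, so no number affected is claimed. The primary endpoint, the analysis and the sample size of 506 do not depend on this. The incomplete safety sentence is a minor wording matter.

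The conclusion rests on the printed table and sections only. If the full protocol already has a rule above 80, the remedy is to print it.

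**What to change.** 1. In Table 4, Group A, bound the fourth row as > 30 to < 60 ng/ml.
2. Add a row for > 80 ng/ml: hold, or no more than 1000 IU/day, and re-evaluate at 3 months. State that supplementation stops above 100 ng/ml, the level the document itself calls excess, in addition to the existing stop for signs or symptoms.
3. In the Interventions and toxicity sections, say that 4000 IU/day is the maximum daily maintenance dose and excludes the 25,000-75,000 IU given at study visits under Table 4.

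The exact value of 10 ng/ml, which matches no Group A row, and the overlap of the two lowest Group B rows can be tidied in the same edit.

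The cost is low: two table rows, a few sentences and a note to sites. No visit, assay or analysis changes.
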